## Abstract

**Background:**

Well-being is a multidimensional concept and has been extended to many areas. Student well-being has garnered attention over the last decade due to concerns that have been raised. Digital health interventions have the potential to enhance and improve student well-being.

**Objective:**

The objective of the study is to design, develop, and pilot-test a digital health platform to enhance student well-being.

**Methods:**

A sample size of 5000 participants will be recruited across Gujarat and Tamil Nadu, India. Students will be enrolled from Parul University in Vadodara, Gujarat, as well as Panimalar Medical College Hospital and Research Institute, Panimalar Engineering College, Panimalar Institute of Technology, and Panimalar College of Nursing in Chennai, Tamil Nadu. Current undergraduate and graduate students consenting to participate will be recruited using convenience sampling from these institutes. The study will collect baseline data to construct the student well-being index. Based on the risk profile, a random subset of the population will be provided access to the digital health intervention, which will deliver tailored interactive messages addressing the various dimensions of well-being among undergraduate and graduate students. The eligible study participants will be aged 18 years and older, enrolled in these institutes, and willing to give their consent to participate in the study.

**Results:**

The proposed research is an unfunded study. The enrollment of the individuals in the study began in October 2022. Data gathered will be analyzed using SAS (version 9.3; SAS Institute) and results will be reported as 95% CIs and *P* values.

**Conclusions:**

The proposed study will help to determine the factors affecting well-being among college students and help in designing digital health interventions to improve the well-being of undergraduate and graduate students.

**International Registered Report Identifier (IRRID):**

PRR1-10.2196/39779

## Introduction

### Background and Rationale

Well-being is a multifaceted concept that encompasses 3 dimensions: mental, social, and physical [1]. According to the World Health Organization, “Health is a state of complete physical, mental and social well-being and not merely the absence of disease or infirmity” [2]. Therefore, well-being can be summarized as a positive outcome that constitutes physical, mental, and social stability. It comprises the presence of positive emotions such as happiness and resilience and the absence of negative emotions such as anxiety and depression [3].

Over the last decade, there has been an increased interest in student well-being [4]. The transitional period from school to university puts forward many new challenges and changes for students, such as academic demands, facing new people, making independent choices, and being away from home and social networks. These shifts or changes act as potent stressors in the lives of students [5].

In a survey conducted by the World Health Organization in 21 countries to assess the associations of mental disorders with college entry and attrition, it was found that anxiety disorders were the most prevalent class of disorders, followed by mood disorders, substance disorders, and behavioral disorders [6]. Another cross-sectional study conducted across 30 low- and middle-income countries drew similar conclusions [7]. A study of undergraduate students at a South African university reported minimal to mild symptoms of depression in 87.7% of students and moderate to severe symptoms in 11.2% of students. Similarly, low anxiety was prevalent in 84.2% of students, and moderate to severe anxiety was present in 5.8% of students [8]. Additional studies in Nigeria and Kenya also reported that moderate to severe depression was prevalent among university students [9,10].

For medical education students, the components of a stressful environment include on-call responsibilities, high workload, competitive training, peer pressure, a large volume of content to study, and financial burdens [11]. A meta-analysis reported depression in approximately one-third of medical students globally [12], which may contribute to anxiety, burnout, suicidal thoughts, and substance abuse [11].

In a local context, a survey to assess the perceived stress and psychological well-being of 281 college students from 6 states in India showed a negative effect of perceived stress on their psychological well-being. A higher level of internet addiction negatively affected psychological well-being, whereas perceived social support from friends, family, and significant others was positively associated with well-being among college students [13]. Female students reported a higher level of well-being even though their stress levels were similar to male students [14].

In a study conducted by Jeyaraj et al [15] among college students in Maharashtra, India, stress was observed in 24.4% of students. Moderate to severe stress was experienced by 14.4% of students. Academic factors and lifestyle were significantly associated predictors of stress among college students. Another large survey study in India highlighted that more than 80% of medical students experienced burnout and were at higher risk of mental disorders and lower well-being [16]. This was also corroborated by additional studies that reported high psychological distress, burnout [17], perceived stress [18], poor well-being, stress, and depression in Indian medical students [19,20].

In India, mental health problems are prevalent in the young adult population, and since India is home to the world’s largest population of young people, it has become a matter of critical concern [21]. The World Health Organization reported that 8% of the Indian population has common mental disorders, of which 4.5% and 3.5% experience depression and anxiety, respectively [16].

However, conventional evidence-based psychological treatments have certain limitations associated with them, such as lack of access, stigma, and difficulty in affording the services [22]. Additionally, the limited availability of mental health professionals exacerbates the situation [23]. In this scenario, digital health interventions have the potential to address these challenges as they can reach a larger audience, are more cost-effective, and avoid the risk of stigma [24]. Targeted use of technology can be more effective in the health and well-being domain [25]. Various digital interventions, including computer-based [26,27], web-based [28,29], mobile-based (SMS text message–based and app-based), and virtual reality–based [30-32] interventions have been used for depression, anxiety, stress, sleep quality, psychological well-being, and mindfulness.

There is limited research available on digital health interventions in enhancing overall well-being among college students in India [33]. Further studies have shown that use of the health belief model (HBM) for student well-being is effective [34]. Hence, this study aims to explore factors affecting the well-being of students and develop and design a tailored, internet- and mobile-enabled digital health intervention based on the HBM to enhance well-being among college students in Indian settings.

### Study Objective

The objective of the study is to design, develop and pilot-test a digital health platform to enhance student well-being. The study aims are (1) to identify multiple determinants and factors impacting well-being among undergraduate and graduate students; (2) to design and develop a digital health intervention based on the HBM, incorporating the findings of aim 1 to address the well-being issues among undergraduate and graduate students; (3) to evaluate the feasibility and acceptance of the proposed digital health intervention; and (4) to evaluate the role of the digital health intervention, as well as the roles of adherence to and engagement with it, in enhancing the well-being of undergraduate and graduate students.

## Methods

### Study Design and Population

For aim 1, a cross-sectional study will be conducted to identify multiple determinants affecting the well-being of the students. Five thousand participants will be recruited across Gujarat and Tamil Nadu, India. Current undergraduates and graduates will be recruited from Parul University in Vadodara, Gujarat, as well as Panimalar Medical College Hospital and Research Institute, Panimalar Engineering College, Panimalar Institute of Technology, and Panimalar College of Nursing in Chennai, Tamil Nadu, using a convenience sampling approach. The participants will be recruited from their respective institutes with prior permission from their departments. The survey will be filled out by the students using their mobile devices or from the computer labs of the institutes. The survey will consist of validated tools, which are described in Multimedia Appendix 1 [35-37].

For aim 2, we will use a mixed methods approach and a quasi-experimental research design to gather data. Baseline data will be collected from aim 1 using predefined questionnaires and validated tools. Additionally, 3 focus group discussions (FGDs) will be conducted at each study site to identify the barriers that students face to manage their well-being. Two focus groups at each site is considered to be ideal [38]. Consenting participants from the baseline survey will be invited via an email to participate in the FGDs; they will then be given access to the mobile- and web-based platform to generate their initial user profiles. The data gathered from user profiles and FGDs will be used to formulate a student well-being index and also used to design and develop a tailored and context-specific digital health intervention (based on the principle of a human-centered approach) to address the well-being issues of the students. The quantitative data collected from the baseline survey and the qualitative factors will help in identifying causal factors in the environment of the students affecting their well-being [39]. The digital intervention will be based on a human-centered approach and will be designed after understanding an analysis of responses generated from the baseline survey and FGDs. The digital health intervention will be designed as per the needs identified from the FGDs and the baseline survey with population health informatics.

For aim 3 and aim 4, we will perform a randomized controlled trial. Based on the well-being index generated, high-risk individuals will be divided randomly into an intervention group and a control group. The digital health intervention will be a mobile- and web-based platform for students designed to provide tailored well-being–related education and awareness. A human-centered approach will be used to design and develop the intervention by incorporating the students’ needs and preferences to ensure an optimal technology-enabled intervention [40]. The study will also use the HBM in designing the digital health intervention, where HBM will be used as a framework to aid in the factors that influence implementation and the persistence of students in maintaining well-being. The HBM is one of the most widely used theoretical frameworks for understanding behavioral change. The model holds that an individual’s likelihood of adopting and maintaining a new behavior is heavily influenced by their perceptions of the health threat and the behavior being proposed to address that threat [41]. The intervention will include modules for the physical, social, and mental well-being of the students. The study participants will be able to access the personalized, human-centered digital health intervention through their computers or mobile phones depending on the technology platform available to them. The intervention will be tailored and will be delivered via interactive messages addressing the various dimensions of well-being among undergraduates and graduate students. Study participants in the control group will be provided with an educational booklet addressing health information related to student well-being. Pre- and postevaluation of the individuals in the intervention and control groups will be conducted to assess the impact of the digital health intervention. The feasibility, adherence, engagement, and acceptability of the system will be assessed.

### Study Eligibility

The eligible study participants will be aged 18 years or older; be enrolled in Parul University, Panimalar Medical College Hospital and Research Institute, Panimalar Engineering College, Panimalar Institute of Technology, or the Panimalar College Of Nursing; have access to a Wi-Fi or internet-enabled device; and consent to participate in the study. Participants younger than 18 years, not enrolled in these institutes, or not providing consent will be excluded from the study.

### Data Collection, Data Entry, and Quality Assurance

To ensure efficiency and high-quality data collection and processing, we will (1) use a well-trained team of field-workers, (2) use a clearly defined study manual, (3) conduct weekly meetings with the research team, and (4) maintain logs of all patient contacts. Confidentiality of the information obtained from the participants will be ensured. The information will be accessible to members of the research team only.

### Variable Assessment

#### Sociodemographic Profile

Data will be gathered from the participants on age, gender, income level, education level, region of residence, marital status, children, and religion. The socioeconomic status of the participants’ families will be evaluated with an updated version of the original Kuppuswamy Scale [42].

#### Health Status Profile

The height and weight of the participants will be measured to calculate BMI, as Sarwer and Polonsky [43] suggested that BMI has an impact on well-being. Any self-reported disability will be assessed. Predefined questionnaires will be used to gather the data.

#### Familiarity With Technology

We will gather data on access to desktop or laptop computers, tablets, and mobile phones, as well as the type of phone possessed, knowledge of texting, and access to and familiarity with the internet. Predefined questionnaires will be used to gather the data.

#### Health Behavior

Health behavior data will include the consumption of tobacco, use of alcohol, smoking, and sleep duration. Predefined questionnaires will be used to gather the data.

#### College Profile

Data will be collected on the residential status and prior education of the students (within the city or outside the city). Predefined questionnaires will be used to gather the data.

### Data Security and Privacy

Data security will be maintained by frequent backup in password-protected computers locked in the principal investigator’s office. The information will be accessed by the research team only. Locked data will be stored for 5 years from the point of study completion, at which time they will be destroyed [44].

### Outcomes

The study will help to identify multiple determinants affecting the students’ well-being. Additionally, it will explore the role of digital health interventions in enhancing good health and well-being among the students. The study will also help in designing and developing individualized, tailored, and interactive internet-enabled digital health interventions to manage the well-being of undergraduate and graduate students.

### Outcome Variables

The outcomes will be assessed with the tools described in this section.

#### General Well-Being

The General Well-Being Schedule will be used to gather data. The scale covers 6 dimensions, including anxiety, depression, general health, positive well-being, self-control, and vitality, to measure mental and physical well-being [45].

#### Perceived Social Support

The Multi-Dimensional Scale of Perceived Social Support will be used to collect the data. It includes subscales for support from family, friends, and significant others to assess perceived social support [46].

#### Mental Well-Being

Two components will be measured to assess mental wellness: stress and depression. Depression will be measured via the 8-item Patient Health Questionnaire [47] on a 4-point Likert scale that ranges from 0 (“not at all”) to 3 (“nearly every day”). Stress will be measured through the 10-item Perceived Stress Scale [48], which ranges from “never” to “very often” on a 5-point Likert scale.

#### Family Demands

Family demands are measured through a work-family conflict scale. It has 5 items on a Likert scale, from 1 (“strongly disagree”) to 7 (“strongly agree”) [49].

#### System Acceptability

System acceptability will be evaluated through the Client Satisfaction Questionnaire–8 to assess the acceptability of the digital health intervention [35].

#### General Self-Efficacy

General self-efficacy will be evaluated through the General Self-Efficacy Scale [36]. It is a 10-item scale to assess the ability to cope with daily challenging demands or situations in life.

#### Stigma

The Stigma Scale will be used to assess stigma. It has 42 statements on a 5-point Likert scale, ranging from “strongly agree” to “strongly disagree” [37].

#### Perceived Ease of Use

The Perceived Ease of Use questionnaire will be used to assess the feasibility of the digital health intervention [50].

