#### Other Tools, Follow-Up, and Engagement

Tools other than the Perceived Ease of Use questionnaire and Client Satisfaction Questionnaire–8 will be used before and after the digital health intervention to assess its usefulness. Individuals will be followed up for a period of 3 months at regular intervals to assess adherence to the well-being modules provided in the digital health intervention. Engagement with the digital health intervention will be assessed by monitoring the number of weekly logins, completion of tasks in a timely manner, and submission of regular data.

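### Aim 3 feasibility is assigned to an ease-of-use questionnaire, a usability rating that cannot by itself register non-uptake, non-completion or dropout; the usage data that could are placed under other constructs.

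*Protocol article*

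**What the plan says.** All references are to the protocol article.

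- **Study Objective.** Aim 3 is "to evaluate the feasibility and acceptance of the proposed digital health intervention". Aim 4 concerns the role of the intervention, "as well as the roles of adherence to and engagement with it, in enhancing the well-being" of students.
- **Perceived Ease of Use** (under Outcome Variables). "The Perceived Ease of Use questionnaire will be used to assess the feasibility of the digital health intervention". No other section names a feasibility measure.
- **System Acceptability.** "System acceptability will be evaluated through the Client Satisfaction Questionnaire–8". So the other half of aim 3 also rests on a self-report questionnaire.
- **Other Tools, Follow-Up, and Engagement.** On timing, this section states: "Tools other than the Perceived Ease of Use questionnaire and Client Satisfaction Questionnaire–8 will be used before and after the digital health intervention". The same section says: "Individuals will be followed up for a period of 3 months at regular intervals to assess adherence to the well-being modules". It defines engagement by weekly login counts, timely task completion and regular data submission.
- **Study Design and Population.** "Study participants in the control group will be provided with an educational booklet". The same paragraph lists feasibility, adherence, engagement and acceptability as four separate things to be assessed.
- **Ethical Considerations.** Withdrawals will be included in the final reporting.

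**The concern.** Ease of use is one user's view of a platform. Feasibility, for a study whose stated objective includes pilot-testing that platform, also covers whether students take it up, work through it and remain to the end. The article gives the feasibility label to the first and files the second under different headings. The Discussion itself lists usability and feasibility as distinct properties to be assessed, so the mismatch is visible within the article.

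What is at stake is the answer to aim 3. If that answer is drawn from the named measure, it will be the same for a platform that nearly all allocated students used and for one that few used, provided those who respond give similar ratings. The randomised comparison of well-being outcomes is not affected.

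**Working it through.** The article states no feasibility threshold, expected retention or trial-arm size, so there is no figure of the plan's own to reproduce. (The 5000 participants are recruited for the aim 1 survey and play no part here.) The check is mainly a reading of the sections against each other.

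**Step 1: what is tied to which aim.**

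| Construct | Measure named | Where it is used |
|---|---|---|
| Feasibility | Perceived Ease of Use questionnaire | Aim 3 |
| Acceptability | Client Satisfaction Questionnaire–8 | Aim 3 |
| Adherence | 3-month follow-up of module adherence | Aim 4 |
| Engagement | Logins, timely tasks, data submission | Aim 4 |
| Withdrawals | Reported in the final analysis | Not linked to an aim |

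No sentence makes any of the last three rows part of the feasibility assessment.

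**Step 2: who can supply the named measure.** The control group has no platform to rate. The questionnaire is outside the before-and-after set, and Table 1 schedules a post-deployment assessment of the intervention in months 14-15. The reasonable inference is that it is completed after exposure, by intervention-arm students who respond. The article does not say this outright.

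**Step 3: what the measure can and cannot show (illustration, all inputs assumed).** Assume *N* = 200 allocated to the platform, a fraction *r* who respond, and 80% of responders rating it easy to use. The article gives no scoring or cut-off for the questionnaire, so the yes/no split is also an assumption. Then:

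- responders *m* = *rN*; favourable responders *x* = 0.80 × *m*
- responder-only share = *x*/*m*
- favourable ratings per allocated student = *x*/*N*, with Wilson 95% CI
- share if every non-responder would have been favourable = (*x* + *N* − *m*)/*N*

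| *r* | *m* | *x* | *x*/*m* | *x*/*N* (95% CI) | (*x* + *N* − *m*)/*N* |
|---|---|---|---|---|---|
| 20% | 40 | 32 | 80% | 16% (11.6 to 21.7) | 96% |
| 40% | 80 | 64 | 80% | 32% (25.9 to 38.8) | 92% |
| 60% | 120 | 96 | 80% | 48% (41.2 to 54.9) | 88% |
| 80% | 160 | 128 | 80% | 64% (57.1 to 70.3) | 84% |
| 100% | 200 | 160 | 80% | 80% (73.9 to 85.0) | 80% |

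The responder-only column does not move with *r*: the named measure carries no information on take-up or retention. The last two columns bracket the share of all allocated students who would find the platform easy. At *r* = 20% the bracket is 16% to 96%, with the responder figure of 80% inside it, so non-response alone does not fix the sign of any bias.

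**Step 4: one scenario with a direction.** If 70% abandon the platform and 20% of them would rate it easy, against 80% of the 30% who continue, the figure over everyone is 0.30 × 0.80 + 0.70 × 0.20 = 0.24 + 0.14 = 38%, against 80% among those who continue. This shows that a large difference is possible, not that it is expected.

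**The case against.** The strongest reply is that abandonment is already measured and will be reported. Logins, task completion, data submission and 3-month adherence are all collected, and withdrawals will appear in the final analysis. On that view the complaint is about which heading the counts sit under. It can be added that the article does not say ease of use is the *sole* basis for feasibility, and that denominators, intervals and response fractions are details an article may leave to the full protocol or analysis plan.

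Much of this stands, and it rules out several stronger readings that a reader might infer:

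- *That abandonment would be hidden, or that a platform most students drop would be declared feasible.* Usage and withdrawals will be on record, and the article contains no threshold or go/no-go rule under which such a declaration would be made.
- *That only students still using the platform are asked.* The text does not say so; someone who logged in once and stopped could still rate it. Restriction to exposed responders is an inference, and restriction to continuing users goes further than the inference allows.
- *That the feasibility result is biased upward.* This is plausible, but nothing in the documents establishes direction or size.
- *That the percentages above describe this trial.* None of their inputs comes from it.

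What does not stand is the claim that this is only omitted detail. The article itself chose the instrument for feasibility, named no other, and assigned the usage data elsewhere. That is a stated choice, and it does not fit the aim.

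**Conclusion.** The point holds in a limited form. The only measure named for aim 3 feasibility is a usability rating that, by itself, cannot reflect non-uptake, non-completion or dropout. The data that could do so are already planned but are assigned to engagement and adherence. The consequence is a named aim answered by a measure too narrow for it, not a loss of data.

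No size can be given from the documents. In the illustration (200 allocated, 80% of responders favourable), the named measure stays at 80% while favourable ratings per allocated student range from 16% to 80%. The conclusion rests on two inferences, that the questionnaire follows exposure and that only intervention-arm responders complete it; no section contradicts either. It is worth correcting because the repair is cheap and lets the study answer its own question.

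**What to change.** 1. In the Perceived Ease of Use section, describe the questionnaire as a measure of usability.
2. Assess aim 3 feasibility with data already planned, each on the allocated denominator with a 95% CI:
   - share of allocated intervention students with at least one login;
   - share of allocated intervention students completing modules or tasks;
   - share of each arm with a post-evaluation at 3 months (taking the post-evaluation to fall at the end of the stated follow-up).
3. Report the ease-of-use and Client Satisfaction Questionnaire–8 scores together with the fraction of allocated intervention students who answered.
4. Where invitation counts are kept, also report the share of invited high-risk students who enter the trial. This is optional, because the article describes no separate invitation to the randomised stage.

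Sending both questionnaires to students who stopped using the platform would be useful but is also optional: the article describes no such tracing, so it would be added fieldwork.

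**Cost.** Items 1 to 3 need rewording and a little more analysis, with no new data collection. The drawback is that the feasibility figure may be less favourable than an ease-of-use score.
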